### Study design

This exploratory sequential mixed-methods study will be divided into five phases, which are described below.

Table 2 shows the enrollment, interview, intervention, and assessment schedule. This protocol was developed and reported following the Standard Protocol Items: Recommendations for Interventional Trials (SPIRIT), and the clinical trial will be carried out and reported in accordance with the Consolidated Standards of Reporting Trials (CONSORT).

**Table 2 Tab2:**
[figure not shown]
Schedule of enrollment, interviews, intervention, and assessment of the Educational Intervention trial, following the Standard Protocol Items Recommended for Clinical Trials (SPIRIT) guidelines

^a^Age, marital status, number of deliveries, economic status, etc

^b^The main measurable effective variables of the I-Change model

### Procedures

#### Phase 1: the qualitative exploration: understanding women’s perspective

The qualitative research will take 6 months to complete. Understanding the perceptions of women toward CC preventive behavior will be explored using semi-structured interviews with open-ended questions and directed qualitative content analysis methods. The interview will begin with semi-structured questions based on the I-Change model as a theoretical framework [32]. Then the probing questions, following the interviewee’s answers, lead the researcher to explain women’s perceptions and preventive behaviors about cervical cancer prevention. For example, the interview begins with a general question “What have you done so far to avoid cervical cancer?” and continues with guiding questions such as Can you give an example? or “Do you have any experience?”

The interviews will take place face-to-face in a quiet environment that is mutually convenient for both parties. In accordance with the study’s goals and objectives, an interview guide has been created. The first question is a broad, open-ended inquiry about CC preventive behaviors, to which they will be asked to respond in detail. Then, based on the answer, more probing questions will be asked. The goal is to gain a comprehensive understanding of women’s perceptions and behaviors about CC prevention. Each interview will be transcribed in its entirety after it is completed. To ensure that the researcher has accurately interpreted the participants’ statements, the transcripts will be sent to each participant (member check) along with a summary of key topics from each interview. The sample size of the interview process will depend on the information saturation rule which means as the sample expands, no new theme will be induced from the information the participants supplied.

#### Phase 2: requirement prioritization—providing experts’ perspective

Realized findings from phase 1 (QR) will provide all perceptions of participants toward CC preventive behaviors. After all, *the Analytic Hierarchy Process* (AHP) [33] will be run to provide us with a rational framework for a needed decision by quantifying its criteria and alternative options, and for relating emerged themes and constructs to the overall goal. The main outputs of this phase will be resulted in *prioritizing* the main measurable effective variables of the I-Change model [32]. The next step will be processed for the development and psychometrics of an assessment tool regarding selected constructs.

#### Phase 3: development and psychometric of tool assessment

The tool that will be used to collect the data is a questionnaire which will be designed based on achievements from previous phases. Then, the initial tool will be ready for the psychometric process.

#### Phase 4: app framework and content development

Based on our previous studies and references reviewing, preliminary functional modules of the app will be collected. The next step of this study is to search and evaluate currently existing domestic cervical cancer/HPV prevention-related apps on App Store and Android Market. We use the words “HPV/ sexually transmitted disease/Cervical Cancer” respectively to search for related apps. Each eligible app will be downloaded and its features, including names, download numbers, target population, and main function modules, will be listed and analyzed. Personal face-to-face interviews with periodical experts and focused group sessions will hold to discuss the framework of the app from the interactivity, feasibility, acceptability, and user experience aspects. Finally, the functional modules of the app will be determined. The application that is going to be made is based on the Android platform, and since the main language of the Android operating system is Java, it will be made with the Java programming language. The app will be developed by a company that specialized in mobile application development. After the app development is completed, 30 participants will be invited to test it, and necessary modifications will be made according to their advice.

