### Requirement

First, participants will be recruited via an online call through the virtual platforms such as Instagram pages, WhatsApp, and Telegram channel. Candidates will communicate with the trained research assistant (SK; the first author) through the phone number included in the announcement. Then, the research assistant explains the purpose of the study by phone for women who are eligible to enter the study. She will obtain contact information from potential trial participants. The assent will be sent via email or any social media messenger such as Telegram or WhatsApp. Table 1 contains a complete list of the inclusion and exclusion criteria.

**Table 1 Tab1:** Inclusion and exclusion criteria

Inclusion criteria	Exclusion criteria
Women aged 18–49 years Married (having at least one sexual relationship experience) Being the residence of North Iran during the study Tend to participate with informed consent to share information, and participate Women own a smartphone and the ability to use it Women without mental disorders, drug dependence, and addiction	Absence of more than two sessions in training sessions Having a special illness that prevents participants to take part in training sessions Woman who is not interested in the subject of the curriculum

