#### Phase 5: the randomized controlled trial for effectiveness evaluation of the app-based intervention

##### Intervention description

This study is a parallel-group randomized controlled trial. Eligible participants are randomized in a 1:1:1 allocation ratio to one of three groups: two experiment groups, in which women receive the application (app) and digital book. The training contents in both experimental groups outlined preventive behaviors of CC regarding I-Change model constructs retrieved from phases one and two. In another word, group A will be called mobile app group and group B will be called the Digi booklet-group and will receive the same training content in different ways (Fig. 1).

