**Fig. 1 Fig1:**
[figure not shown]
The flow chart of the randomized controlled protocol

Each of the participants in experiment groups A and B will be required to register as a user to download the mobile-App and Digi booklet separately. The educational content will be based on the latest national and international guidelines for the prevention of CC of information (facts).

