## Limitation

Our study may face several limitations. As it is an open study and participants are aware that they are entering into an intervention entitled in cervical cancer prevention behaviors, bias is likely in the study results. Then, a random allocation of participants can help achieve a balance in sociodemographic characteristics. Another limitation of this study is the need to use self-reporting tools, and the possibility of memory error, lack of clarity, socio-cultural concerns, and individual biases affecting the results are inevitable. Last but not least, our study may have dropouts during the enrolment phase of the CONSORT process because some participants might not have access to a smartphone and the time extension for enrollment to achieve the estimated sample size is probable.

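### The app is described for Android phones, but eligibility asks only for a smartphone, so some women could be randomised to the app arm with no stated way to receive it

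*Protocol article*

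**What the plan says.** Under Phase 4 the article states: "The application that is going to be made is based on the Android platform". It gives Android as the reason for programming in Java and mentions no iOS or web version. The same section plans a search of "prevention-related apps on App Store and Android Market", so the authors know that more than one phone platform is in use.

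The device criterion in Table 1 (section Requirement) is "Women own a smartphone and the ability to use it". It names no operating system, and the text introducing the table says that the list of criteria is complete.

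Under Phase 5, participants are "randomized in a 1:1:1 allocation ratio to one of three groups". Those in groups A and B are "required to register as a user to download the mobile-App and Digi booklet separately". The Limitation section expects losses at enrolment "because some participants might not have access to a smartphone"; it does not mention phone type. Among the exclusions, Table 1 lists "Absence of more than two sessions in training sessions", which can only be observed once the intervention is under way.

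**The concern.** The eligibility criterion is wider than the group that the described app can serve. The article does not mention screening for operating system, stratifying by it, lending a phone or offering another route to the app. A woman with a non-Android phone who follows the plan as written can reach group A and be unable to install its intervention.

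What follows depends on how she is handled:

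- **Kept and analysed in group A.** She contributes a control-like outcome to the app arm, and the app-versus-control difference shrinks.
- **Lost, or removed after allocation** (the exclusion for missed sessions is one possible route). Group A then loses women defined by phone type while similar women stay in group C, and the randomised comparison is no longer like with like.

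The app-versus-booklet comparison is exposed in the same way if the booklet runs on other phones, which the article does not state.

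**Working it through.** **Inputs from Sample size and power calculations:** alpha 0.05 (two-sided, since the formula uses z at 1 − α/2), power 0.80, 61 per group before dropout, 15% dropout, 70 per group recruited.

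**Assumptions:**

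- The share f of group A unable to install the app is not given; 2% to 20% is shown.
- These women gain nothing and are analysed in group A.
- The two groups have equal SDs.

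**Step 1. The plan's own figure.** 61 / (1 − 0.15) = 71.8, or 72; 61 × 1.15 = 70.15, or 71. The stated 70 lies within two women of either. The 61 itself cannot be reproduced, because the means and SDs come from a cited study and are not shown.

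**Step 2. Implied effect.** With equal SDs the formula is n = 2(1.960 + 0.842)² / d². Solving at n = 61: d = 2.802 × √(2/61) = 0.507.

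**Step 3. Dilution.** The diluted effect is 0.507 × (1 − f). Power at 61 per group is Φ(0.507 × (1 − f) × √(61/2) − 1.960). The number needed to restore 80% power is 61 / (1 − f)², rounded up.

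| f (assumed) | Women of 70 | Diluted d | Power at 61 | Evaluable per group to restore 80% |
|---|---|---|---|---|
| 0 | 0 | 0.507 | 80% | 61 |
| 2% | 1.4 | 0.497 | 78% | 64 (63.5) |
| 5% | 3.5 | 0.482 | 76% | 68 (67.6) |
| 10% | 7 | 0.457 | 71% | 76 (75.3) |
| 20% | 14 | 0.406 | 61% | 96 (95.3) |

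Allowing for the extra variance from mixing two kinds of women in group A lowers power by at most one percentage point (75.6%, 70.8% and 60.2% at 5%, 10% and 20%).

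**Step 4. If these women are lost instead.** The dilution figures then do not apply. The dropout allowance in group A is 0.15 × 70 = 10.5 women. Non-installers would take 3.5 of these at f = 5% and 7 at f = 10%; at f = 20%, 14 would exceed the allowance. The resulting bias cannot be sized, because the article does not say how outcomes differ by phone type.

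**The case against.** The strongest reply has five parts.

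1. **Android only is an inference.** The article says what the app is based on and never says that other phones are shut out. That is correct. What stands is that no other version or route is described, and group A must download the app to receive it.

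2. **The check may exist in a fuller document.** The Requirement section describes a telephone contact before consent, and the Limitation section places device-access losses at enrolment. But the article presents Table 1 as the complete criteria, and the table sets a device requirement that does not match the app. This is a criterion set too wide, not a detail left out for brevity.

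3. **The size is hypothetical.** This stands. Neither the share nor the effect size is in the article, and the calculation also assumes no effect at all in non-installers. Power is evaluated at 61, after the dropout allowance. At all 70 recruited and with no other dropout, the same formula gives about 81%, 77% and 67% at 5%, 10% and 20%.

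4. **Dilution is not bias.** This also stands. Analysed as randomised, the trial validly estimates the effect of offering this app to smartphone owners. The cost in that case is power and a smaller effect.

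5. **Selection bias and the contrast with the booklet are conditional.** A reader might infer that non-installers will be replaced after allocation, or that the booklet opens on any phone. The article says neither. Groups A and B both register and download, and the booklet's format is not stated.

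**Conclusion.** The mismatch is real and worth correcting. As written, the criteria can place a woman in group A with no stated way to receive its intervention. The consequence is either dilution of app versus control, or selective loss from group A relative to group C (and to group B only if the booklet works on other phones).

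The size is uncertain. Power falls to about 76%, 71% or 61% at assumed shares of 5%, 10% or 20%, given d of about 0.507 and no effect in non-installers. At 2% the loss is under two percentage points. It would go too far to conclude that the trial is underpowered by a known amount or that its comparison is biased: the article gives no share of non-Android phones and no rule for removing or replacing these women.

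**What to change.** For women still to be enrolled, reword the device criterion in Table 1 to owning a smartphone able to run the study app (Android, unless another version is provided). Check it in the screening call, before randomisation, for all three arms, so that the groups stay comparable. Keep women already randomised in their allocated arm for analysis, whether or not they could install the app.

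The cost is one reworded criterion, one screening question, a slightly narrower population and somewhat slower recruitment. Trial status reports that recruitment opened in October 2021 and is continuing, so this is also a mid-recruitment amendment to be communicated to the relevant parties, and it cannot alter the eligibility of women already enrolled. Providing a version for other phones would avoid narrowing the population, at the price of further development.

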#### Phase 5: the randomized controlled trial for effectiveness evaluation of the app-based intervention

##### Intervention description

This study is a parallel-group randomized controlled trial. Eligible participants are randomized in a 1:1:1 allocation ratio to one of three groups: two experiment groups, in which women receive the application (app) and digital book. The training contents in both experimental groups outlined preventive behaviors of CC regarding I-Change model constructs retrieved from phases one and two. In another word, group A will be called mobile app group and group B will be called the Digi booklet-group and will receive the same training content in different ways (Fig. 1).

**Fig. 1 Fig1:**
[figure not shown]
The flow chart of the randomized controlled protocol

Each of the participants in experiment groups A and B will be required to register as a user to download the mobile-App and Digi booklet separately. The educational content will be based on the latest national and international guidelines for the prevention of CC of information (facts).

##### Control group

Group C as the control group will receive no training content during the study. Following the ethical issue, they only will be provided with educational materials at the end of the intervention procedure. They will receive routine care, such as free health information brochures and free counseling services as needed.

### Sample size and power calculations

The sample size was determined by the primary objective (comparison of participation in the experiment and control groups, respectively) and women will be allocated in equal numbers to the three randomization groups. Following the study conducted [34], the sample size we require in the quantitative phase to provide sufficient power was calculated as 61 persons for each group. This sample size was calculated to be adequate at an alpha of 0.05 and a power of .80, to test for a difference between the groups. We considered a potential dropout rate of 15%. According to the formula below, we should start with a recruitment target of 70 participants in each group: $${n}_1={n}_2=\frac{\left({s}_1^2+{s}_2^2\right){\left({z}_{1- {\propto }\!\left/ \ {2}\right.}+{z}_{1-\beta}\right)}^2\ }{{\left(\mu {\mu}_2\right)}^{2.}}$$

In line with this approach, a total of 210 women aged 18–49 years will be recruited using the inclusion and exclusion criteria listed in Table 1. Participants will be allocated into three groups (the two intervention groups plus one control group).

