### Outcome measures

The initial research questions addressed in this study are “Does the educational intervention based on the I-Change model via mobile app affect CC preventive behaviors among Iranian women?”. To answer this main question, the following primary outcomes are expected:Determining and comparing the effects of an educational intervention designed based on the I-Change model via a mobile app knowledge related to CC prevention in women in the target and control groups before, immediately, and 3 months after the interventions.Determining and comparing the effects of an educational intervention designed based on the I-Change model via a mobile app on information factors related to CC prevention in women in the target and control groups before, immediately, and 3 months after the interventions.Determining and comparing the effects of an educational intervention designed based on the I-Change model via a mobile app motivation to CC prevention in women in the target and control groups before, immediately, and 3 months after the interventions.Determining and comparing the effects of an educational intervention designed based on the I-Change model via a mobile app predisposing factors to CC prevention in women in the target and control groups before, immediately, and 3 months after the interventions.Determining and comparing the effects of an educational intervention designed based on the I-Change model via a mobile app behavioral intention to CC prevention in women in the target and control groups before, immediately, and 3 months after the interventions.Determining and comparing the effects of an educational intervention designed based on the I-Change model via a mobile app action to prevent for CC prevention in women in the target and control groups before, immediately, and 3 months after the interventions.

Consequently, we expect the effect of our educational intervention on preventive action regarding CC among women. To assess the expected secondary outcomes, a self-reported assessment addressing preventive actions (using a condom, doing pap-test and genital examination) will be conducted.

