#### Phase 5: analysis of intervention outcomes

To ensure that the data is correctly entered, a double-entry of data will be performed by two different individuals. All data obtained from women will be entered into SPSS software. A code will be defined to identify missing data. The obtained data will be kept strictly confidential and will be stored with secured and restricted access; also, the signed consent will be kept locked. Follow-up data are received using the same questionnaires as used at baseline. The intervention will be evaluated based only on Pap smear completion 3 months after the enrollment and baseline survey. Data will be summarized with descriptive statistics (mean, median, standard deviation, percentiles for numerical variables, frequencies, and percentages for categorical variables). To determine the normality of data, Smirnov and Kolmogorov will be used. Determining the frequency of demographic information in both groups is analyzed using descriptive statistics templates. To analyze the quantitative variables, the independent *t*-test and paired *t*-test are analyzed. To compare the mean score, the quantitative (intra-group) variables of the two groups of the test and control groups before and after the intervention were used as independent samples. To compare the means, the quantitative (inter-group) variables were compared between the two groups of control and test before and after paired *t*-test intervention is used. In the case of non-normalization, the mean score of the quantitative (intra-group) variables in the two groups of the test and control groups is used before and after the intervention in Mann-Whitney. To compare the meanings, the quantitative variables (inter-group) were used in both control and test groups before and after the Wilcoxon test. To determine the relationship between the underlying and dependent variables in the case of normal, the Pierson correlation test is used and the Spearman correlation test will be used to determine the relationship between the underlying and dependent variables in the case of normal. To analyze the qualitative variables, a chi-square test is used to analyze the qualitative variables. The significance level in this study is considered to be 0.5. The information obtained will be used by the related statistical software, including SPSS version 23.

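### The stated 80% power with 61 women per group is not shown for Pap smear completion, and three sections disagree on which outcome the trial is sized for and judged on

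*Protocol article*

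**What the plan says.** All three places are in the protocol article.

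- **Sample size and power calculations.** The objective is given as: "The sample size was determined by the primary objective (comparison of participation in the experiment and control groups, respectively". With a reference to an earlier study, it continues: "the sample size we require in the quantitative phase to provide sufficient power was calculated as 61 persons for each group". This number is called "adequate at an alpha of 0.05 and a power of .80, to test for a difference between the groups". The printed formula has two variances in the numerator and a squared expression in means in the denominator. A 15% dropout allowance follows, and then: "According to the formula below, we should start with a recruitment target of 70 participants in each group". No mean difference, standard deviation, control rate or target rate is given.
- **Phase 5: analysis of intervention outcomes.** "The intervention will be evaluated based only on Pap smear completion 3 months after the enrollment and baseline survey". The same section plans t-tests (or rank tests) for quantitative variables and a chi-square test for qualitative ones.
- **Outcome measures.** The six listed primary outcomes are I-Change measures: knowledge, information factors, motivation, predisposing factors, behavioural intention and action. Pap testing comes after them: "To assess the expected secondary outcomes, a self-reported assessment addressing preventive actions (using a condom, doing pap-test and genital examination) will be conducted".

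**The concern.** The formula sizes a comparison of mean scores. The objective it is said to serve reads as uptake: the sample size section does not define participation, but the Background section on cervical cancer in Iran uses participation rate for Pap test uptake. The analysis section then makes a binary outcome the sole basis for judging the intervention. The power figure and the deciding outcome are thus on different scales, and nothing in the article links them.

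The stake is how a null result would be read. The Discussion treats greater adherence to screening as what success would mean. If Pap completion shows no significant difference, a reader who relies on the stated 80% may conclude that the app does not work, although a gain of 10 or 15 points could easily have been missed.

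**Working it through.** **Inputs from the article:** 61 per group; alpha 0.05, taken as two-sided because the formula uses z(1−α/2); power 0.80; 15% dropout; 70 per group, 210 in total. **Assumptions:** one pairwise comparison without multiplicity adjustment, and the control rates below. The Background reports Pap participation of 27.1%, 50% and 58.6% in Iranian studies and 5% for developing countries. These are background figures, not 3-month uptake among volunteers, so they serve only to span a range; 10%, 20% and 41.4% fill it in.

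**1. Can 61 be reproduced?** No, because no effect or SD is stated. It can only be solved backwards. With (1.960 + 0.842)² = 7.849 and equal SDs, n = 2 × 7.849 / d², so d = 2.802 × √(2/61) = 0.507. As a check, d = 0.51 gives 61 and d = 0.50 gives 63. The article does not state this standardised difference.

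**2. What 61 per group gives for a yes/no outcome.** Pooled-variance two-proportion test, with p̄ = (p₁ + p₂)/2:

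power = Φ{ [ |p₂ − p₁|√n − 1.960 √(2p̄(1 − p̄)) ] / √(p₁(1 − p₁) + p₂(1 − p₂)) }

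Example, 27.1% against 37.1%: (0.100 × 7.810 − 1.960 × 0.660) / 0.656 = −0.78, so power is about 22%.

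| Assumed control rate | Rate needed for 80% power, n = 61 | Rise (points), n = 61 | Rise (points), n = 59 | Power for +10, n = 61 | Power for +20, n = 61 | n per group for +10 |
|---|---|---|---|---|---|---|
| 5% | 22.2% | 17.2 | 17.6 | 45.2% | 88.1% | 141 |
| 10% | 30.1% | 20.1 | 20.5 | 33.8% | 79.6% | 199 |
| 20% | 43.4% | 23.4 | 23.8 | 24.5% | 67.8% | 294 |
| 27.1% | 51.6% | 24.5 | 25.0 | 21.7% | 63.1% | 341 |
| 41.4% | 66.4% | 25.0 | 25.4 | 19.6% | 60.1% | 390 |
| 50% | 74.4% | 24.4 | 24.7 | 19.7% | 61.8% | 388 |
| 58.6% | 81.6% | 23.0 | 23.3 | 20.7% | 66.6% | 363 |

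**3. The printed formula used for proportions.** Putting s² = p(1 − p) turns it into the unpooled two-proportion formula. For 27.1% against 51.1%: (0.1976 + 0.2499) × 7.849 / 0.240² = 61. So 61 per group is compatible with 80% power for Pap completion, but only for a difference of this order.

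**4. Dropout.** 61 / 0.85 = 71.8, so 72 per group would be needed. 70 × 0.85 = 59.5, and 70 covers only 1 − 61/70 = 12.9% loss. The stated 70 matches 61 × 1.15 = 70.15. If 61 gives exactly 80%, then at 59.5 the power is Φ(0.507 × √(59.5/2) − 1.960) = 79.0%, and at 59 it is 78.7%.

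**The case against.** The strongest reply is that nothing has been shown to be miscalculated. A reader might infer that the 80% is false for Pap completion. The documents do not support that: they state no rates and no target difference, the inputs lie in a cited study that is not at hand, and step 3 shows that the same formula gives 61 for a rise of about 24 points from 27.1%. What can be said is that the 80% is not shown for this outcome. Nor does the text settle whether 17 to 25 points is an unrealistic gain, since it names no target.

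Second, the Outcome measures section makes construct measures primary. For scores from the Phase 3 questionnaire a two-means formula is suitable, and the planned t-tests fit it. On that reading the faults are the word participation in the sample size section and the sentence that makes Pap completion the sole basis of evaluation. This stands as a possible resolution. It does not remove the problem, because the three sections still contradict each other and the power cannot be judged until they agree.

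Third, reading participation as a proportion is an inference from the Background, and the control rates are assumed. Both are true. The contradiction with the analysis section does not depend on the first, and the conclusion holds at every rate in the table.

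Fourth, multiplying by 1.15 is a common shortcut that leaves the target two women per group short. It is a slip, but a minor one, and it does not carry the point.

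**Conclusion.** The concern holds as a mismatch between outcome, formula and power statement, not as proof of an underpowered trial. The stated 80% power with 61 per group is not tied to Pap smear completion. For that outcome it would apply only to a rise of about 17 to 25 percentage points, depending on a control rate assumed between 5% and 58.6%. A 10-point rise would have about 20% to 45% power. These figures assume a two-sided 0.05 test of one pair of arms. The dropout slip lowers power by about 1 point. If the construct scores decide the trial, the means formula is appropriate, and the error lies in the wording of the sample size and analysis sections.

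**What to change.** Keep 210 women. Reconcile Outcome measures, Sample size and power calculations, and the Phase 5 analysis section so that all three name the same deciding outcome. Then:

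- **If Pap completion decides:** replace the means formula with a two-proportion calculation, and state the assumed control rate and the detectable difference at about 59 evaluable women per group (about 18 to 25 points over the range above).
- **If a construct score decides:** correct the reference to participation and the sentence making Pap completion the only basis of evaluation. State the mean difference and SDs taken from the cited study; the back-solved 0.507 should not be written in as if it had been planned. Give the power at about 59 evaluable per group (about 79% if 61 was exactly 80%), and acknowledge the low power for Pap completion.

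In either case, say that 70 randomised less 15% leaves about 59 per group. The cost is wording only, with no added recruitment. The downside is that the stated power or detectable effect becomes less favourable.

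### With 15% dropout, 70 women per group leaves 59 to 60, slightly fewer than the 61 the protocol says it needs; the effect on power is about one percentage point

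*Protocol article*

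**What the plan says.** All the figures are in the protocol article under Sample size and power calculations.

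- The requirement "was calculated as 61 persons for each group", described as "adequate at an alpha of 0.05 and a power of .80, to test for a difference between the groups".
- On losses: "We considered a potential dropout rate of 15" per cent.
- On recruitment: "we should start with a recruitment target of 70 participants in each group". The text attributes this target to the formula printed beneath it.
- In total, "a total of 210 women aged 18–49 years will be recruited", which is 3 x 70. The Intervention description confirms equal allocation to the three groups.

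The printed formula is the usual one for comparing two means. It contains variances, a difference in means and two normal quantiles, but no dropout term. The section gives no means or standard deviations and refers to a cited study for the basis of the 61.

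**The concern.** A dropout rate is ordinarily read as the fraction of recruited women who are lost. On that reading the recruitment target should be large enough that 61 remain after 15% have gone, and 70 is not. The required number, the dropout rate and the target then cannot all be met, and the printed formula does not show how 70 was reached.

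What is at stake is the accuracy of the power statement. The 61 is presented as the number required, and the allowance exists to protect it. The protocol commits the trial to CONSORT reporting, so the sample-size statement is likely to be carried into the results paper. Some loss after randomisation is also plausible: Table 1 lists missing more than two training sessions as an exclusion criterion, which can apply only once training has begun.

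**Working it through.** **Inputs, all from Sample size and power calculations.** Evaluable women per group 61; alpha 0.05, two-sided because the printed formula uses the quantile at 1 - alpha/2; power 0.80; dropout 15%; target 70 per group.

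**Reproducing the 70.**

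- Adding 15% to the requirement: 61 x (1 + 0.15) = 70.15, which rounds down to 70. Rounding up would give 71.
- Dividing by the retained fraction: 61 / (1 - 0.15) = 71.76, so 72 per group and 3 x 72 = 216 in total.

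Only the first route gives the stated figure. The document does not state which was used.

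**What 70 delivers.**

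- Remaining after 15% loss: 70 x 0.85 = 59.5, so 59 or 60 women per group, 1 to 2 short of 61.
- Largest loss that still leaves 61: (70 - 61)/70 = 9/70 = 12.9%.
- Rounding of the 61 does not close the gap. If the unrounded requirement was just over 60, then 60/0.85 = 70.6, still more than 70.

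**Effect on power.** The effect size is not given, so it has to be back-solved. This is an assumption, and two versions bracket it.

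*61 gives exactly 80%.* Normal formula: d = (1.960 + 0.842) x sqrt(2/61) = 0.507. Power at n per group is Phi(d x sqrt(n/2) - 1.960). At n = 59.5: Phi(0.507 x sqrt(29.75) - 1.960) = 0.790. Using the t-test throughout, 61 per group gives 80% at d = 0.511, and power at 59.5 is again 0.790.

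*61 was rounded up from just over 60.* Here d = 2.802 x sqrt(2/60) = 0.511 by the normal formula.

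| Women remaining per group | Power if 61 gives exactly 80% | Power if 61 was rounded up from just over 60 |
|---|---|---|
| 59 | 78.7% | 79.3% |
| 59.5 | 79.0% | 79.7% |
| 60 | 79.3% | 80.0% |

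At the expected 59.5 the loss is 0.3 to 1.0 percentage points. The largest loss in the table is 1.3 points, with 59 remaining and 61 giving exactly 80%.

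**The case against.** The best defence is that the gap is trivial and partly a matter of convention. If the 15% is an allowance added to the 61, the figures agree apart from rounding 70.15 down. That convention is common, if inexact, and the text calls the rate only a potential one. A planning guess of this kind is more uncertain than the difference between 12.9% and 15%. The shortfall against 72 is 2 women per group, 6 of 216 overall (2.8%), and no decision about the trial turns on it.

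Most of this stands, and it limits the point to a small correction. It does not remove it: the text calls the 15% a dropout rate, and on the ordinary meaning 70 leaves fewer than 61 however the 70 was reached. Nothing else in the document reconciles the figures.

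Three stronger readings are tempting and are not supported:

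- *That the allowance was demonstrably applied the wrong way round.* The match with 61 x 1.15 makes this plausible, but the method is not stated, and 70 could simply be a convenient round target.
- *That the trial is materially underpowered.* The loss is about one point, on an effect size that the protocol does not give.
- *That power falls to 78.4%.* This figure results from back-solving the effect with the normal formula (0.507) and then evaluating it with a t-test. The same mixture gives only 79.4% at the full 61, so about 0.6 of the apparent 1.6-point loss comes from changing method, not from dropout.

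**Conclusion.** The point holds as a minor inconsistency. With 15% of recruited women lost, 70 per group leaves 59 to 60, not the 61 stated as required. Seventy supports the 61 only up to 12.9% loss. These statements use the protocol's own figures and need only the usual meaning of a dropout rate.

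The size in terms of power is conditional. It assumes a two-sided two-group comparison of means and an effect back-solved from the 61. On that basis power is about 79.0% at 59.5 per group if 61 gives exactly 80%, by either the normal or the t-test calculation, and about 79.7% if 61 was rounded up from just over 60. A reader might infer that the design fails or that more women must be recruited; a difference of this size supports neither. What needs correcting is the statement.

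**What to change.** Keep 210 women and restate one sentence in Sample size and power calculations, in one of two ways:

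- 70 per group allows for about 13% dropout (9/70 = 12.9%) while retaining the 61 needed for 80% power; or
- with 15% dropout about 59 to 60 women per group remain, and power is about 79% under the assumptions behind the 61.

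The sentence should also say how the allowance was applied, because the printed formula does not include it. Only if the sponsor wishes to keep both 15% and 80% would the target become 72 per group, 216 in total, which is 6 more women.

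Either restatement changes no recruitment number, analysis or trial conduct. The cost is a stated dropout tolerance or power that is slightly less favourable than the present one.
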